#### In situ simulation

Four months after the intervention, the effect of training on team performance will be measured by so-called unannounced (as far as possible) in situ simulations, during which care providers are assessed on their teamwork within their own working environment. The in situ simulation will consist of one or two scenarios which will be managed by a team consisting of primary and secondary care providers, located at a delivery room in the hospital. The in situ simulation will be videotaped and analysed by independent experts.

### Hypothesis

Multiprofessional simulation-based obstetric team training, using CRM and elements of DP, will improve perinatal outcome, team performance, quality of care as perceived by patients and collaboration of care providers.

Questions to be answered:

1. Does multiprofessional simulation-based obstetric team training improve perinatal outcome?

2. Does multiprofessional simulation-based obstetric team training improve team performance as assessed by an unannounced in situ simulation?

3. Does multiprofessional simulation-based obstetric team training improve quality of care as perceived by patients?

4. Does multiprofessional simulation-based obstetric team training improve collaboration of care providers?

### Outcome measures

Primary outcome will be a composite adverse perinatal outcome as defined by perinatal mortality and/or NICU admission. Data on the primary outcome will be obtained from the Netherlands Perinatal Registry (PRN).

Secondary outcomes will be:

1. 1.Team performance. For measuring team performance, an independent panel of experts will evaluate the videotaped team training sessions and calculate the Clinical Teamwork Scale (CTS) [53].

2. Quality of care as perceived by patients. This will be measured before and after the training by using a questionnaire consisting of the validated PCQ and some additional questions regarding pregnancy, delivery and the first postpartum week [28].

3. Care providers’ satisfaction with teamwork and collaboration between and within the different levels of care. This will be measured before and after the training using a questionnaire which is partly based on the validated Doctors’ Opinions on Collaboration (DOC) questionnaire for general practitioners and medical specialists and adjusted to the obstetric care field [54].

4. Incidence of:

a. Big 4 disorders defined as [18]:

Small for gestational age, defined as a birth weight below the 10^th^ percentile

Preterm delivery before 37 weeks

Congenital anomalies

Five minute Apgar score below 7

b. number of Big 4 pregnancies starting delivery in primary care

c. perinatal mortality

d. fetal mortality rate

e. neonatal mortality rate

f. NICU admission

g. admission to neonatology unit (non-NICU)

h. caesarean section

i. ventouse or forceps delivery

j. episiotomy

k. hemorrhage postpartum (>1000 ml of blood loss)

l. third or fourth degree perineal trauma

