The scenarios are based on national and international guidelines [41-52]. Prior to the training, teams will receive an explanation concerning the equipment and environment. Each trainee will participate actively in at least one scenario and often more. Each scenario will start with an introductory briefing video. Thereafter, the team moves to the simulation room where they manage the simulated patient. State of the art high fidelity patient simulators will be used (Noelle™ and Newborn Hal™, Gaumard, Miami, Florida) and patient actresses. All scenarios will be videotaped (using B-Line Medical® software, Washington, DC). After each scenario a debriefing with reviewing the video recordings will be provided. The instructors will provide feedback on teamwork and skills (medical technical and non-technical) using video recordings. Learning goals based on CRM will be evaluated during the debriefing, such as: attention situational awareness, self-awareness, leadership, assertiveness, decision-making, flexibility, adaptability, and communication tools. There will be a focus on standardised communication and handovers based on the SBAR system (Situation, Background, Assessment, Recommendation).

The nine elements of DB will, if achievable, be applicated to the training by:

1) A syllabus concerning communication tools, CRM and medical knowledge about Big 4 disorders has been written and will be handed out prior to the training. To stimulate the motivation and concentration of the trainee a multiple choice exam prior to the training will be performed.

2) Learning objects:

a. prior to the training, all trainees will be asked to define an individual learning goal

b. learning goals will be defined per specific scenario and will be evaluated during the debriefing

c. take home messages will be hand over to the teams at the end of the training. The teams will work on implementing learning goals in their Obstetric Cooperation.

3) This training will not sufficiently be able to focus on an (individual) appropriate level of difficulty. In general, the scenarios have an increasing difficult level.

4) This training is a one-time training making focused and repetitive practice not achievable. However, to achieve repetitive awareness and use of communication tools based on CRM and SBAR, the study groups will use pocket charts with communication tools in daily practice.

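### The team-performance outcome is scored on training-day videos while question 2 asks about in situ performance, and no contrast is stated from which improvement could be judged

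*Protocol article*

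**What the plan says.** Three parts of the protocol article's Methods bear on team performance.

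- **Hypothesis, question 2**: "Does multiprofessional simulation-based obstetric team training improve team performance as assessed by an unannounced in situ simulation"?
- **In situ simulation**, with the time point set at four months after training: "the effect of training on team performance will be measured by so-called unannounced (as far as possible) in situ simulations". The simulation has one or two scenarios, "managed by a team consisting of primary and secondary care providers, located at a delivery room in the hospital". On assessment, the section says: "The in situ simulation will be videotaped and analysed by independent experts". It names no scale.
- **Outcome measures, secondary outcome 1**: "an independent panel of experts will evaluate the videotaped team training sessions and calculate the Clinical Teamwork Scale (CTS"). The in situ simulation is not mentioned here.

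Under Recruitment and intervention, the training is a one-time, one-day event at a simulation centre in Eindhoven. On its recordings, that section states: "All scenarios will be videotaped".

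In the same outcome list, items 2 (quality of care as perceived by patients) and 3 (care providers' satisfaction with collaboration) are each said to be measured both before and after the training. Item 1 carries no such statement.

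**The concern.** A question about improvement needs an outcome that captures what is being asked and a contrast against which to judge it. Here the question and the outcome definition point to different recordings, made on different occasions and in different places, and neither comes with a stated comparator.

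The training-day videos show teams while they are being trained, with a debriefing after each scenario. Scores from them reflect practice and feedback within the day, not whether anything carries over to the workplace. The in situ videos are the ones that could show transfer to work, but the only time point given for them is after training. The evaluation model that the Background adopts runs from learning through changed behaviour to patient outcome. The in situ simulation is where behaviour at work would be observed, so it matters which recordings carry the outcome.

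**Working it through.** No arithmetic applies: the point rests on no sample size, power or event figure. The check is a comparison of the text.

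**Step 1. Set the descriptions side by side.**

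| | Hypothesis, question 2 | In situ simulation | Outcome measures, item 1 |
|---|---|---|---|
| What is observed | In situ simulation | In situ simulation | Training sessions |
| When | Not given | Four months after training | During training |
| Where | Not given | Hospital delivery room | Simulation centre (from Recruitment and intervention) |
| Raters | Not given | Independent experts | Independent expert panel |
| Scale | Not given | Not named | CTS |
| Contrast | Implied by the word improve | None stated | None stated |

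The first two columns agree. The third differs from them in occasion and place, and it alone names an instrument.

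**Step 2. Could the training sessions in the outcome list mean the in situ simulations?** Not on a natural reading. Training is held at the simulation centre and its scenarios are filmed there. It happens once, so there is no later training session that could supply a follow-up score. The in situ simulation is a separate event with its own section and its own filming.

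**Step 3. Follow each description to its result.**

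- Outcome list followed: CTS scores from within the intervention. These do not answer a question framed on in situ performance.
- In situ section followed: scores on an unnamed scale, after training only. These describe post-training performance and cannot show change.

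**Step 4. Is the missing contrast only the brevity of an article?** Partly it could be. But the same list takes the space to give before-and-after timing for items 2 and 3, so team performance stands out as the exception.

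**Step 5. Could footage already planned supply a baseline?** The first filmed scenario of each training day precedes any debriefing and could be set against the in situ video. The article does not propose this, and its own facts limit such a comparison:

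- The setting differs: simulation centre against hospital delivery room.
- The cases differ: the four training scenarios are set or begin at home.
- Training scenarios generally become harder through the day, so the first would tend to be among the easier ones.
- A syllabus and a multiple-choice exam come before the training, so teams are not unexposed.
- A trainee need be active in only one scenario, so the active members may differ.
- Raters would recognise the setting, so masking would be largely nominal.

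**Step 6. Does the design offer anything stronger?** Yes. In the stepped wedge all groups start untrained and switch in sequence, so in situ simulations could be run in groups not yet trained. None is described.

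**The case against.** The strongest reply is that the two measurements can coexist. Both sets of videos are planned, both go to independent experts, and the similar wording leaves room for one panel scoring both. A reader might infer that the definitions are incompatible; the article does not support that. What stands is narrower: the outcome text omits the in situ simulation, the in situ section names no scale, and nothing says how the two are to be used together.

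A second reply is that silence is not exclusion. The full protocol may contain a baseline in situ simulation, and a reader might wrongly take the article to establish that none will be made. The supportable statement is that none is described. The explicit before-and-after timing of items 2 and 3 keeps the point alive.

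A reader might also infer a count: four groups with one or two scenarios each, hence 4 × 1 = 4 to 4 × 2 = 8 in situ scenarios. That assumes one simulation per group. The article speaks of simulations in the plural, of several training teams within a group, and gives no number of in situ simulations per group. No such figure should be used.

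Finally, if a pre-post comparison can be built from planned videos, question 2 is not beyond any answer. That is fair, but the available comparison is weak for the reasons in step 5, and the plan would have to state it. It does not remove the mismatch between question and outcome.

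**Conclusion.** The point holds as a mismatch between question 2 and the outcome assigned to it, together with the absence of a stated comparator. As the article is written, one route gives scores from within the intervention and the other gives post-training scores with nothing to compare them with. Neither supports a conclusion that training improves in situ team performance.

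No numerical size can be attached, because the number of in situ simulations is not given. In scope, it affects one of the four research questions and the first-listed secondary outcome. The primary outcome of perinatal mortality or NICU admission, its sample size and its mixed-model analysis are untouched. It should be corrected, but it does not threaten the main result.

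The conclusion assumes that the training sessions in the outcome list are the simulation-centre sessions, which the rest of the Methods supports, and that no comparator is fixed in a fuller document not shown here. If one is, the article's outcome text still needs to agree with question 2.

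**What to change.** 1. Reconcile the Hypothesis, In situ simulation and Outcome measures sections so that the CTS outcome for question 2 is scored on the in situ videos at four months. If training-day scores are also wanted, list them as a separate, descriptive measure. This costs text, plus CTS scoring of videos already planned.
2. State the comparator. If there is none, limit the conclusion on question 2 to a description of post-training performance. This costs text only.
3. If the first filmed training scenario is to serve as a baseline, say so in advance, have the same panel score both sets of videos, and report the result as an uncontrolled, exploratory pre-post comparison. Name the limits listed in step 5: setting, scenarios, increasing difficulty, prior syllabus and exam, possible change of active members, and largely nominal masking. This costs rating time but no new recordings.
4. If a stronger answer is wanted, add in situ simulations in groups that have not yet been trained, scored by the same panel on the same scale. This uses the staggered roll-out and keeps the setting constant, but it needs extra simulation sessions, staff time and rating.

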### Sample size calculation

In 2010 perinatal mortality rate was 0.9% and the NICU admission rate 2.3%. To avoid double telling, a composite rate of mortality and NICU admission will be around 3%. [5]. The sample size for the study was calculated by using the formula as proposed by Woertman and De Hoop [38]. This formula calculates the design effect required on top of the sample size calculation for a standard randomised clinical trial (RCT). To show a reduction in perinatal mortality and NICU admission rate from 3% to 1.65%, with an alpha of 0.05 and a power of 80%, a total of 4,000 deliveries would be needed for a simple RCT design. The design effect was calculated assuming an intracluster correlation (ICC) of 0.05, a cluster size of 1,800 deliveries per year, and four clusters or study groups. Taking into account the design effect, we need 565 deliveries per measurement period per cluster. To achieve this number we need 16 weeks for each period, adding up to a total study period of 82 weeks including a 16-week control period before the first training. A mixed effects model will be used to model the data and test the hypothesis of no effect from team training to accommodate cluster effects and time effects. Statistical significance will be accepted at a two-sided p-value < 0.05. In the study region 9,000 deliveries occur per year, with a minimum of around 1,806 deliveries per year per study group (cluster) and a maximum of around 3,500.

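### The ICC of 0.05 has no stated source or scale; beside a 3% event rate it implies an implausible spread between groups, and 565 deliveries per cluster-period do not give the stated 80% power under any reading examined

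*Protocol article*

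**What the plan says.** All of this is in the protocol article, Methods, Sample size calculation.

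- Event rate: "a composite rate of mortality and NICU admission will be around 3"%.
- Target: "To show a reduction in perinatal mortality and NICU admission rate from 3% to 1.65%, with an alpha of 0.05 and a power of 80"%. Before clustering, "a total of 4,000 deliveries would be needed for a simple RCT design".
- Clustering (cut one word short): "The design effect was calculated assuming an intracluster correlation (ICC) of 0.05, a cluster size of 1,800 deliveries per year, and four clusters or study".
- Result: "we need 565 deliveries per measurement period per cluster", collected in 16-week periods over 82 weeks including one control period, which makes five periods.
- Analysis: "A mixed effects model will be used to model the data and test the hypothesis of no effect from team training", with allowance for cluster and time effects, two-sided at 0.05.
- Volume: 9,000 deliveries a year in the region; groups range from about 1,806 to 3,500.

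The Design subsection places the study groups in a single sub-region. Under Recruitment and intervention, the tertiary centre's region was used for the pilot and is not one of the four clusters.

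**The concern.** The ICC is the only statement in the calculation about how much the groups differ. For a rare binary outcome its meaning depends on its scale. The cited method multiplies a two-proportion sample size by a design effect, so its ICC is the between-cluster share of p(1-p). Read that way, 0.05 is very large beside a 3% rate and hard to reconcile with the same fall from 3% to 1.65% in every group.

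If the groups really differed that much, most events would come from one or two of the four, and the training effect would be hard to separate from calendar time. A null result would then be read as coming from a trial with 80% power when the design did not have it.

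**Working it through.** **1. The unadjusted total.** Two proportions, 3% against 1.65%, two-sided 0.05, power 80%: 3,904 (unpooled variance) to 3,910 (pooled). The stated 4,000 reproduces within 3%.

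**2. What the ICC implies.** On the proportion scale, SD = sqrt(ICC × p(1-p)) = sqrt(0.05 × 0.03 × 0.97) = 0.0381, or 3.8 points around a mean of 3%. If group rates followed a beta distribution with that mean and ICC, Beta(0.57, 18.43), the 10th, 50th and 90th percentiles would be 0.08%, 1.6% and 7.9%. About 46% of groups would lie below 1.35%, where a 1.35-point drop cannot occur. The beta shape is an assumption; the SD is not.

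**3. The design effect.** The article does not print the formula. Its standard form, with k = 4 steps, b = 1 baseline period, t = 1 measurement per step and n per cluster-period, is

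DE = [1 + ICC(ktn + bn - 1)] / [1 + ICC(ktn/2 + bn - 1)] × 3(1 - ICC) / [2t(k - 1/k)].

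At ICC 0.05 and n = 565: (142.2 / 85.7) × (2.85 / 7.5) = 0.6305. Then 4,000 × 0.6305 / 4 = 630 per cluster-period (616 starting from 3,910; 632 with n = 1,800 in the formula). The stated 565 does not reproduce from these inputs.

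| ICC | DE at n = 565 | n per cluster-period from 4,000 |
|---|---|---|
| 0.001 | 0.567 | 567 |
| 0.005 | 0.635 | 635 |
| 0.01 | 0.645 | 645 |
| 0.05 | 0.631 | 631 |

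From 0.005 to 0.05 the formula barely moves, so it gives no warning about the ICC.

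**4. Power at 565 with ICC 0.05.** Four clusters, five periods, 3% control rate. The simulations use a constant odds ratio of (0.0165/0.9835)/(0.03/0.97) = 0.54 and period effects. Cluster effects are fitted as fixed unless stated.

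| Reading | Power |
|---|---|
| Proportion scale, logistic model (beta or logit-normal group rates) | 51-58% |
| Proportion scale, random-intercept logistic (200 runs, Monte Carlo SE about 3.5 points) | 43% (beta), 58% (logit-normal) |
| Proportion scale, linear model | 64-67% |
| Hussey-Hughes, variance at the control rate of 3% | 65.9% |
| Logit scale (SD 0.42, about 0.005 on the proportion scale) | 72-74% |
| Hussey-Hughes, variance at the mean rate of 2.325% | 76.5% |

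**5. How much is due to the ICC.** By Hussey-Hughes with mean-rate variance at ICC 0.05, going from 565 to 630 raises power from 76.5% to 80.8%; that part belongs to the 565 figure. With no heterogeneity and fixed cluster effects, simulated power at 565 is about 75%. This is not a general ceiling: a random-intercept model also uses between-cluster information when the groups hardly differ, and gave about 91.5% with no heterogeneity (200 runs). Hussey-Hughes with mean-rate variance gives 80.7% at ICC 0.001, but 76.2% at 0.005 and 75.5% at 0.01.

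**6. At the region's volume.** With 9,000 deliveries a year, split by assumption into about 1,806, 1,847, 1,847 and 3,500:

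| Assumed ICC | Power |
|---|---|
| 0.001, proportion scale | 82-83% |
| 0.005-0.01, proportion scale | 75-79% |
| 0.05, logit scale | about 80% |
| 0.05, proportion scale (logistic) | 57-65% |

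**The case against.** The strongest reply has four parts.

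- **The scale is supplied by the reader.** The article does not say proportion scale, and 0.05 on the logit scale is an ordinary spread. This stands, and it is why the scale must be stated. The logit reading still gives only 72-74% at 565, and the cited formula does not work on that scale.
- **The low simulated figures partly reflect the set-up.** Drawing four independent group rates lets the regional average drift from the planned 3%. Holding it within 0.3 points of 3% gives about 59% (logistic) and 75% (linear) at 565. So for a linear model most of the apparent loss goes once the planned rate is respected; for a logistic model a loss remains.
- **The ICC does not drive the required number.** Within the formula, replacing 0.05 by 0.005-0.01 would slightly raise it. This stands. A reader might infer that a smaller ICC alone restores 80% at 565; in that range it does not.
- **A condensed article may omit the source of an ICC.** True, and the omission alone would be minor. Here the article prints the ICC, the event rate and the power together, and they do not fit.

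Two stronger readings are also tempting. One is that 0.05 is unusable as an input; with the scale unstated, the document does not support that. The other is that the trial's power is 51-66%; that band is conditional on the proportion scale and on the assumed group rates or control-rate variance. The infeasible 1.35-point drop in 46% of groups likewise rests on the beta shape, and does not arise under a constant odds ratio.

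**Conclusion.** The point holds in a limited form. The ICC of 0.05 is unsourced, its scale is unstated, and on the scale of the formula it feeds it implies a spread of 3.8 points around 3%. Nothing in the article supports that for neighbouring groups without the tertiary centre; calling it implausible is a judgement from the size of the spread, not from registry data.

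At 565 per cluster-period the stated 80% is missed under every reading of ICC 0.05 examined, from about 76% in the most favourable to the low fifties or below in the least. How far it is missed depends on the scale, the shape of the group rates and the variance used. Some of the shortfall comes from 565 being about 8-11% below what the stated inputs give, which is a separate error. At the actual regional volume the design may still reach about 80%, if the groups differ much less than 0.05 implies on the proportion scale.

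**What to change.** In the sample size paragraph:

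1. State the scale and source of the ICC.
2. Estimate it from the pre-trial rates of the four study groups in the Netherlands Perinatal Registry, and show power over a range of values. The values in the last table are illustrations, not documented figures.
3. Restate power by simulating the planned binary mixed model with the four groups' actual delivery numbers.
4. If 0.05 on the proportion scale is kept, report the power it gives in place of 80%.

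The cost is one reworded paragraph and one short simulation, using the registry that already supplies the primary outcome. No extra enrolment is asked for. The downside is that the restated power may be below 80%.

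### The planned 565 deliveries per cluster per period does not follow from the stated inputs; about 616 to 631 does, and 565 in every cluster gives about 74–76.5% power, not 80%

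*Protocol article*

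**What the plan says.** The point rests on the section *Sample size calculation* of the protocol article.

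- Event rates: "a composite rate of mortality and NICU admission will be around 3"% under control, and the aim is "To show a reduction in perinatal mortality and NICU admission rate from 3% to 1.65"%.
- Error rates: "with an alpha of 0.05 and a power of 80"%; the test is two-sided ("Statistical significance will be accepted at a two-sided p-value < 0.05").
- Individually randomised size: "a total of 4,000 deliveries would be needed for a simple RCT design".
- Stepped-wedge inputs: "The design effect was calculated assuming an intracluster correlation (ICC) of 0.05, a cluster size of 1,800 deliveries per year, and four clusters". The design-effect formula is cited but not printed.
- Result: "Taking into account the design effect, we need 565 deliveries per measurement period per cluster".
- Calendar: "To achieve this number we need 16 weeks for each period, adding up to a total study period of 82 weeks", of which the first 16 weeks are a control period.

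The same section puts regional volume at 9,000 deliveries a year, with a smallest cluster of about 1,806 and a largest of about 3,500. The *Design* section has all clusters starting in the control condition and switching at successive time points, and the caption of Figure 3 confirms four clusters.

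**The concern.** Both the inputs and the result of the design-effect step are printed, so the step can be checked, and it does not reproduce. To get from 4,000 to 565 per cluster-period, the design effect would have to be 565 × 4 / 4,000 = 0.565. The stated ICC and layout give about 0.63.

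The figure matters because the 80% power claim for the primary outcome, the period length and the study duration are all derived from it. A reader cannot tell whether the ICC, the layout or the arithmetic is the part that is wrong.

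**Working it through.** **Step 1: the simple trial.** For 3% against 1.65%, two-sided 0.05, 80% power, the two-proportion formula with pooled variance under the null gives a total of 3,910 (3,904 to 3,906 with unpooled variance, depending on rounding). The plan's 4,000 is this figure rounded up by 2 to 3%. This step reproduces.

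**Step 2: the layout.** Four clusters crossing one at a time give k = 4 steps. One control period gives b = 1, and one measurement per step gives t = 1. That makes five periods, which matches the total duration: 565 / 1,800 × 52 = 16.3 weeks, and 5 × 16.3 = 81.6 weeks.

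**Step 3: the design effect.**

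`DE = [1 + ρ(ktn + bn − 1)] / [1 + ρ(ktn/2 + bn − 1)] × 3(1 − ρ) / [2t(k − 1/k)]`

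With ρ = 0.05 and n = 565:

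- numerator: 1 + 0.05 × (2,260 + 565 − 1) = 142.2
- denominator: 1 + 0.05 × (1,130 + 565 − 1) = 85.7
- last factor: 3 × 0.95 / (2 × 3.75) = 0.38
- DE = 142.2 / 85.7 × 0.38 = 0.6305

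The choice of n hardly matters: DE stays between 0.629 and 0.632 for n from 360 to 1,800. An unclear meaning of cluster size therefore cannot explain 565.

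**Step 4: deliveries per cluster-period**, N × DE / 4, solved so that n agrees with itself:

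| Simple-trial total | Per cluster-period |
|---|---|
| 4,000 (as stated) | 631 |
| 3,910 (pooled) | 617 |
| 3,906 (unpooled) | 616 |
| 3,830 (arcsine) | 604 |
| 4,202 (continuity-corrected) | 663 |
| 3,080 (one-sided) | 485 |

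None is within 3% of 565.

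**Step 5: power at 565 from the design effect.** The effective total is 4 × 565 / 0.6305 = 3,584. Taking 4,000 as exactly 80%, power is Φ(2.80 × √(3,584/4,000) − 1.96) = 75.6%. Working from the event rates directly, it is 76.5%.

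**Step 6: a check that does not use the cited formula.** Take a linear mixed model with random cluster and fixed period effects, I = 4 clusters and T = 5 periods. Let U be the number of treated cluster-periods, W the sum over periods of the squared number of treated clusters, and V the sum over clusters of the squared number of treated periods. Here U = 10, W = 30 and V = 30. The variance of the estimated effect is

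`Var = I·s·(s + Tτ²) / [(IU − W)s + (U² + ITU − TW − IV)τ²]`

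- Total variance at the mean rate: 0.02325 × 0.97675 = 0.02271.
- With the ICC as a share of this total: τ² = 0.05 × 0.02271 = 0.001135, and s = 0.95 × 0.02271 / 565 = 0.0000382.
- The bracketed constants are 40 − 30 = 10 and 100 + 200 − 150 − 120 = 30.
- The standard error is 0.00503, so power is Φ(0.0135 / 0.00503 − 1.96) = 76.5%.
- Power is 80.0% at 617 and 80.9% at 631.
- If the within-cluster variance is set to the full binomial variance instead, power is 74.3% at 565 and 78.9% at 631.

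**Step 7: what would give 565.** From N = 4,000, an ICC of 0.15 gives 566, an ICC of 0.001 gives 567 to 568, and two baseline periods at ICC 0.05 give 568. The first two contradict the stated ICC. Two baseline periods would make six periods, about 6 × 16.3 = 98 weeks, against 82 weeks with a single 16-week control period.

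**Step 8: power on the regional volumes.** The two middle clusters are not given; assume they share the remainder equally: (9,000 − 1,806 − 3,500) / 2 = 1,847 each. Sixteen weeks then yield about 556, 568, 568 and 1,077 deliveries. Over all orders in which the clusters could cross, the Step 6 model gives 82.2% to 83.8% power, or 80.3% to 81.9% under the second variance convention.

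**The case against.** **The trial may have its power anyway.** A reader might infer from the shortfall that the trial is underpowered, or that it must be lengthened: 631 at 1,800 a year is 18.2 weeks per period and about 91 weeks in total. The document does not support that. The 1,800 figure is the size of the smallest cluster applied to all four, the outcome comes from a perinatal registry, and nothing caps the deliveries at 565 per cell. Step 8 shows about 80% to 84% on the section's own volumes. This objection stands, and it limits the point to the stated requirement and the power attached to it.

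**The calendar figures.** It is tempting to add that five periods of 16 weeks make 80 weeks rather than 82, and that 16 weeks at 1,800 a year yield 554 rather than 565. Both come from rounding 16.3 and 81.6 weeks. The 16 and 82 agree with 565 and are not a separate error.

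**How firm the corrected number is.** 631 inherits the rounding of 4,000, and the unrounded total gives about 616. The shortfall of 565 is therefore about 8% (51/616) to 10% (66/631), and a single exact replacement would claim too much precision.

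**What is not visible.** The formula is cited but not printed, Figure 3 is not shown, and one cluster per step is inferred. The inference rests on four clusters, one control period and the total duration, and Step 6 reaches the same conclusion without the cited formula. What cannot be settled is where the error arose: a wrongly entered number of baseline periods is as plausible as a different ICC.

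**Conclusion.** The point holds in a limited form. On the stated inputs, the requirement is about 616 to 631 deliveries per cluster-period. With 565 in every cluster, power is about 74% to 76.5%, some 3.5 to 6 points below the 80% claimed.

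This rests on one cluster crossing per step, one baseline period, one measurement per step, an ICC of 0.05, equal clusters and a normal approximation. The 616 to 631 range takes the ICC as a share of the total variance, as the design effect does.

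It is an error in a planning figure that the primary outcome relies on. It is not evidence that the trial as sized by its region falls short of 80%, although that reassurance depends on the assumed middle cluster sizes and is narrow under the less favourable variance convention.

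**What to change.** Rewrite the sample size paragraph.

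1. Correct the cell size to about 616–631, saying whether it starts from the unrounded or the rounded simple-trial total. If a different ICC or number of baseline periods was actually used, correct that input instead and make the described layout agree with it.
2. Keep the 16-week periods. State power from the expected deliveries in each of the four clusters instead of the 1,800 minimum, giving the four volumes and the variance convention. On the volumes assumed here, that power is about 80–84%.
3. State the number of steps, baseline periods and measurements per step, so that the figure can be reproduced.

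The cost is one corrected paragraph and a short recalculation with the actual cluster volumes. No longer study and no extra recruitment are needed on these figures.
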